#### Plasma and red blood cell fatty acid analyses

Plasma and RBC total lipids will be extracted using the Folch method [43], involving chloroform-methanol (2:1 vol/vol) containing 0.01 % 3,5-di-*tert*-4-butylhydroxytoluene (Sigma-Aldrich, Oakville, ON, Canada) and heptadecanoic acid as an internal standard (Sigma-Aldrich). Extracted fatty acids will be methylated with methanolic HCl. Fatty acid methyl esters will be separated on a SUPELCOWAX 10 capillary gas chromatography column (30 m × 0.25 mm with 0.25-mm film thickness; Supelco/Sigma-Aldrich, Bellefonte, PA, USA) using a gas chromatograph equipped with a flame ionization detector (Bruker 430; Bruker Daltonics, Billerica, MA, USA). Individual fatty acids will be identified by comparison with known standards (Nu-Chek Prep, Elysian, MN, USA). Individual fatty acid levels will be calculated according to the peak area relative to the total area and expressed as a percentage of total fatty acids.

Concentrations of isotope-labeled cholesterol in circulatory cholesterol will be measured over 24 h. In this study, we will measure the deuterium enrichment into RBC cholesterol to calculate FSR of whole-body cholesterol. The initial 24-h interval of D_2_O uptake is considered to be the optimal period for measuring synthesis [44]. The analytical methods for isotope analyses are as follows. For determining cholesterol FSR (%/day), RBC from day 29 and 30 will be saponified with freshly prepared KOH-methanol at 100 °C for 1 h, and the sterol fraction will be extracted with petroleum diethyl ether. RBC cholesterol deuterium enrichment will be quantified using a gas chromatography-pyrolysis-isotope ratio mass spectrometry (Delta V Pulse Isotope Ratio Mass Spectrometer; Thermo Fisher Scientific, Bremen, Germany). Hydrogen gas reduced from water will be analyzed for deuterium enrichment against Vienna Standard Mean Ocean Water [45].

#### Microbiome analysis

Bacterial DNA from the fecal samples will be extracted using the ZR Fecal DNA MiniPrep kit (Zymo Research, Irvine, CA, USA), and DNA concentration and quality will be determined using a NanoDrop 2000c spectrophotometer (NanoDrop Products/Thermo Fisher Scientific, Wilmington, DE, USA). Gut microbial composition will be analyzed by next-generation Illumina-based sequencing (Illumina, San Diego, CA, USA). Briefly, the V3-V4 region of the 16S rRNA gene will be targeted for PCR amplification as described by Fadrosh et al. [46]. PCR products will then be purified using ZR-96 DNA Clean-up Kit (Zymo Research) and added to the MiSeq Reagent Kit V3 (300 cycles; Illumina) for sequencing reactions on a MiSeq platform. The paired-end Illumina fastq files will then be analyzed using the QIIME software package [47]. Principal coordinate analysis will be performed to evaluate the distance matrices by generating two-dimensional plots using PRIMER v6 software (PRIMER-E, Ivybridge, UK).

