## Methods/Design

### Design of the human intervention trial

A randomized, single-blind, crossover trial will be conducted at the Clinical Nutrition Research Unit at the Richardson Centre for Functional Foods and Nutraceuticals (RCFFN), University of Manitoba, Winnipeg, MB, Canada. The study design will consist of four phases with 28 days per phase, and each phase will be separated by 4-week washout periods (Fig. 1). Participants will consume at least one of three daily meals under supervision, along with the treatment foods during weekdays from days 2 to 29 of each phase. Treatment muffins and cookies for the weekend will be packed and provided to participants to take home on Fridays. The other meals will be purchased by the participants from grocery stores on their own. Almost half of the treatments will be consumed under the supervision of a clinical coordinator to ensure optimal compliance. Participants will be instructed to consume no alcoholic or caffeinated beverages. Participants will be instructed not to consume more than one serving of fish or seafood products per month during the study. A 3-day food record will be collected before the study and after each treatment phase. Participants will be strongly recommended to maintain consistency in their physical activities during the experimental period. Compliance with the treatment products will be determined from checklists and by measuring the amount of leftover food if any in the containers returned by the participants the following day.

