### Sample collection

Twelve-hour fasting blood samples will be collected on days 1, 2, 29, and 30 of each intervention phase. Participants will be advised to be fasted for 12 h and not to consume any alcoholic beverage for at least 48 h before blood collection. Participants will also be instructed to refrain from engaging in intense physical activity (aerobic, spinning, and running) for at least 24 h before each visit. On days of blood collection, a checklist with questions on 12-h diet, 48-h alcohol, and 24-h physical activity will be administered and data recorded to determine participant compliance.

Blood samples will be centrifuged at 3000 rpm for 20 minutes at 4 °C; aliquoted to yield serum, plasma, and red blood cells (RBC); and then stored at −80 °C until analyses. To obtain the plasma lipid profile, average values of days 1 and 2 will be considered as baseline and average values of days 29 and 30 will be considered as the endpoint of each treatment phase. In addition, the influence of these diets on gastrointestinal microbial diversity in the current study population will be measured. For this analysis, stool samples (four or five scoops totaling 4 g) will be collected before and after each intervention phase (days 2 and 30) of the trial. Stool sample collection kits, including containers, will be provided for the participants to collect their stool samples. However, it is optional for the participants to provide the stool samples, and they may still participate if they choose not to provide stool samples.

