### Sample size calculation and statistical analysis

Sample size was determined to detect an anticipated difference in LDL-C level of 7.4 % (0.43 mmol/L) due to HOCO consumption, compared with control, with a standard deviation estimate of 0.13 mmol/L. The α and power were taken as 0.05 and 0.8, respectively. A sample size of 35 participants was therefore calculated, with a target of 28 participants, taking into account the block size and the estimated 20 % premature withdrawal rate of participants from the protocol, given the existing level of difficulty in completing the protocol elements.

Statistical analysis will be performed using SAS statistical software (SAS Institute, Cary, NC, USA). Baseline and endpoint measurements will be compared using the analysis of variance (ANOVA) model for determination of treatment effects. The results will be expressed as means with standard errors. The normality of distribution of data will be determined with the Shapiro–Wilk test, and the non-normal variables will be normalized before comparison with other treatment by log transformation. The effects of dietary treatments will be examined using mixed-model ANOVA with diet, sequence, phase, and center as fixed factors and subject as a random factor within the model. Statistical significance will be set at *p* < 0.05 for all analyses. Significance between different dietary effects will be examined with the Bonferroni adjustment for multiple comparisons.

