### Adverse events and concomitant medications

No adverse events due to the study treatments are expected, based on the previous studies [20] and because the experimental components are foods. Adverse events, if any, will be monitored and will be reported in the case report form. All serious adverse events will be reported to sponsors and the institutional ethics board of the University of Manitoba. Serious adverse events will be brought to the attention of the study physician immediately for assignment of attribution. All prescription and over-the-counter medications either used at the start of the trial or initiated during the trial will be recorded.

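### For gut community composition, the only evaluation stated is a descriptive two-dimensional plot, which gives no test of diet and does not use the crossover pairing

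*Protocol article*

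**What the plan says.** The Sample collection section of the protocol article states the aim: "the influence of these diets on gastrointestinal microbial diversity in the current study population will be measured". Stool samples "will be collected before and after each intervention phase (days 2 and 30) of the trial", and "it is optional for the participants to provide the stool samples". The design section gives the number of periods: "The study design will consist of four phases with 28 days per phase".

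The Microbiome analysis section describes the processing, "The paired-end Illumina fastq files will then be analyzed using the QIIME software package", without listing the outputs. It then says how the between-sample distances are assessed: "Principal coordinate analysis will be performed to evaluate the distance matrices by generating two-dimensional plots using PRIMER v6 software". It names no distance measure and no test on the matrices, and says nothing on how samples from the same participant are linked.

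The section on sample size and statistical analysis gives a general rule for diet effects: "mixed-model ANOVA with diet, sequence, phase, and center as fixed factors and subject as a random factor within the model". It sets a 0.05 threshold for all analyses and a Bonferroni adjustment between diets, and it exempts no outcome.

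**The concern.** The article does not leave the evaluation of the distance matrices open. It fixes it as a plot. A principal coordinate plot is a useful picture, but it yields no effect estimate, p-value or error rate. Each contributor may supply up to eight samples. If people differ from one another more than diets do, the first two axes will mostly show people, and a modest diet shift may not be visible. Equally, an apparent cluster could be read as a diet effect with nothing to guard against chance.

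What is at stake is whether the trial can say anything about diet and community composition. The strength of a crossover is comparison within a person, and the stated evaluation of the distance matrices does not use it.

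**Working it through.** **Number of samples.** Four phases × 2 samples = up to 8 per person.
- 35 enrolled: 35 × 8 = 280 samples, of which 35 × 4 = 140 are end-of-phase.
- 28 completers: 28 × 8 = 224 samples, of which 28 × 4 = 112 are end-of-phase.

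These are ceilings because stool is optional. The article gives no microbiome sample size, effect size or power, so there is no figure of its own to reproduce.

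**What each stated method can take.**
- Diversity index or one taxon's abundance: one number per sample. The mixed model applies, with participant random and phase and sequence fixed.
- Distance matrix: one number per pair of samples. The mixed model does not apply directly. Only the plot is stated.

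**Why linking samples matters for a test on distances.** Take total variance 1 per feature, a share r of it between persons, and every person receiving all four diets. With no diet effect, the expected diet sum of squares per feature is 3 × (1 − r), because person differences cancel. If labels are shuffled freely across persons, the reference value is about 3 × 1. The ratio is about 1 − r: 0.7, 0.4 and 0.2 for r = 0.3, 0.6 and 0.8. A test that ignores the person therefore compares the data with far too wide a reference. Shuffling within person removes the mismatch.

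**Illustrative simulations** (end-of-phase samples; every variance share is assumed, none is in the article).

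| Setting | Free shuffle, power | Within-person shuffle, power | Within-person, no effect |
|---|---|---|---|
| A: 28 people, persons 70% of variance | 0–0.5% | 88–99% | 2.5–4.5% |
| A: 28 people, persons 50% | 5–31% | 88–99% | 2.5–4.5% |
| A: 20 people | not reported | 65–96% | 2.5–4.5% |
| B: 28 people, persons 70% | 0% | 97–100% | 5–7% |
| B: 28 people, persons 50% | 3–35% | 94–100% | 5–7% |
| B: 20 people | not reported | 73–99% | 5–7% |
| C: 28 people, r = 0.3 | 0% | 25% | 7% |
| C: 28 people, r = 0.6 | 0% | 59% | 5% |
| C: 28 people, r = 0.8 | 0% | 93% | 3% |

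A: 20 axes, barley shift of 3–5% of within-person variance, 200 trials, 199 permutations. B: the same assumptions with different axis weights. C: 20 features, one diet shifted 0.3 SD on 5 of them, 150 trials, 199 permutations.

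With persons at 70% of variance, the two plotted axes carried about 79% person and 1–2% diet in A, and about 80% and 1% in B.

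C has lower power mainly because its effect is small. The diet variance is 5 × 0.3² × (1/4 × 3/4) = 0.084, against a within-person variance of 20 × (1 − r) = 14, 8 and 4. The shares are 0.6%, 1.1% and 2.1%.

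**The case against.** The strongest reply is that this is a condensed article. The plot is described in a laboratory and bioinformatics paragraph, it is not called the only or the inferential analysis, and a test for a non-primary outcome is ordinary content for an analysis plan that is not shown. That stands as a limit on severity. It does not remove the point, because the article does say how the matrices are to be evaluated, and that method cannot deliver a diet comparison.

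A reader might infer more in three ways, and the documents do not support any of them.

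- **That the question about diet and gut microbes cannot be answered, or that the pairing is lost for the whole microbiome outcome.** The stated aim concerns microbial diversity. Diversity indices and taxon abundances are single variables, and the general mixed model covers them with participant as a random factor. The paired samples are also collected, so a correct multivariate test remains open.
- **That the near-zero power figures describe the plan.** They describe a permutation test that ignores the person, which the article never proposes. They show only why the added test must respect the person. That the plot mostly shows people follows from the assumed person share and is not a fact in the article.
- **That samples taken after antibiotics are wrongly kept.** This would rest on silence, since the article does not define the microbiome analysis set. A rule that drops such samples would also exclude data on an event after randomisation.

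**Conclusion.** The point holds for between-sample community composition only. There the one stated evaluation is descriptive, gives no test of diet and does not use the crossover pairing. Single-number diversity and taxon measures are already provided for.

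Its size is minor. The article names the Framingham score and the blood lipid profile as primary outcomes (Participant feedback section), stool is optional, and no conclusion on the primary outcomes depends on this. The power figures are illustrative. Within-person power ran from about 25% to nearly 100% with 28 people, according to the assumed person and diet shares. What was consistent across the simulations is the direction: ignoring the person cost most or all of the power, whereas shuffling within person kept the false-positive rate at roughly 3% to 7%.

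**What to change.** In the Microbiome analysis section, or in the analysis plan before any ordination is viewed, state:

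*Diet effects on community composition will be tested on end-of-phase (day 30) samples by PERMANOVA on [named distance measure], with participant as a blocking factor and phase in the model. Diet labels will be permuted only within participant. Principal coordinate plots will be descriptive.*

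Another sample set would also serve if it is defined in advance and does not mix baseline and endpoint samples. Permuting labels across all eight samples of a person would mix them.

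Do not add an antibiotic exclusion rule. At most, use information the trial already plans to collect ("All prescription and over-the-counter medications either used at the start of the trial or initiated during the trial will be recorded") for a sensitivity analysis.

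The cost is one paragraph and a few lines of code on distance matrices already planned. No new samples or visits are needed. The downside is a little more analysis work.

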### Sample size calculation and statistical analysis

Sample size was determined to detect an anticipated difference in LDL-C level of 7.4 % (0.43 mmol/L) due to HOCO consumption, compared with control, with a standard deviation estimate of 0.13 mmol/L. The α and power were taken as 0.05 and 0.8, respectively. A sample size of 35 participants was therefore calculated, with a target of 28 participants, taking into account the block size and the estimated 20 % premature withdrawal rate of participants from the protocol, given the existing level of difficulty in completing the protocol elements.

Statistical analysis will be performed using SAS statistical software (SAS Institute, Cary, NC, USA). Baseline and endpoint measurements will be compared using the analysis of variance (ANOVA) model for determination of treatment effects. The results will be expressed as means with standard errors. The normality of distribution of data will be determined with the Shapiro–Wilk test, and the non-normal variables will be normalized before comparison with other treatment by log transformation. The effects of dietary treatments will be examined using mixed-model ANOVA with diet, sequence, phase, and center as fixed factors and subject as a random factor within the model. Statistical significance will be set at *p* < 0.05 for all analyses. Significance between different dietary effects will be examined with the Bonferroni adjustment for multiple comparisons.

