MUFAs, one of the components of canola oil, help reduce CVD risk by lowering blood pressure, blood total cholesterol (TC), and low-density lipoprotein cholesterol (LDL-C) levels; inhibiting LDL-C oxidation [13–16]; and improving glycemic control [17–19]. Oleic acid–enriched canola oil was developed to enhance the health benefits of canola oil related to CVD risk reduction. Its health benefits were compared with regular canola oil in humans in a randomized crossover human trial [12]. In that trial, consumption of HOCO for 28 days was shown to lead to reductions in TC and LDL-C levels and LDL-C/high-density lipoprotein cholesterol (HDL-C) values, as compared with regular canola oil and a control diet without HOCO [12]. The results of a recently completed multicenter randomized controlled trial done at our laboratory validated these findings. In that study, the serum triglycerides (TGs) and 10-year Framingham risk scores, TC/HDL-C and TG/HDL-C ratios, and systolic blood pressure were significantly reduced, and HDL was increased, after consumption of HOCO-DHA compared with regular canola and control diets [20–23].

Consumption of fiber has been indicated to reduce the mortality rate in high-risk CVD populations [24]. β-glucan is a polysaccharide found mainly in yeast, mushrooms, oats, and barley in the form of fiber [25]. β-glucan fibers are located mainly in the endosperm cell walls of cereals. Among cereals, barley and oats are the richest sources of β-glucan, containing 4.0–7.0 % and 2.2–7.8 % wt/wt of β-glucan, respectively, compared with other cereals, such as rye and wheat [26]. Similarly to canola oil, β-glucan has gained significant attention among nutritional researchers because it has been shown to have potentially health-promoting effects in animal and human studies [25, 27]. Consequently, in 1997, the FDA approved a health claim regarding β-glucan from whole oats for reducing the risk of heart disease [28, 29]. More recently, the European Food Safety Authority and Health Canada approved similar health claims for foods containing oats or barley β-glucan [30, 31].

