### Inclusion criteria

Participants aged 18–70 years will be recruited. The participants should be slightly overweight with a body mass index >25 kg/m^2^ and waist circumference >94 cm for men and >80 cm for women in accordance with the International Diabetic Federation MetS criteria for waist circumference. In addition, they have to be deemed to be otherwise healthy by the study physician. Additionally, participants should also meet at least two of the following criteria: (1) TG >1.7 mmol/L, (2) HDL-C <1 mmol/L for males and <1.3 mmol/L for females, (3) fasting glucose >5.6 mmol/L, (4) LDL-C >2.7 mmol/L, and (5) blood pressure >130 mmHg for systolic and >85 mmHg for diastolic.

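### The stated LDL-C difference and standard deviation do not give the target of 28 completers, so the stated 80% power is unsupported as written

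*Protocol article*

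**What the plan says.** In its section on sample size and statistical analysis, the protocol article expresses the planned LDL-C difference twice: as a relative change of 7.4%, and in absolute terms as "0.43 mmol/L) due to HOCO consumption, compared with control, with a standard deviation estimate of 0.13 mmol/L". It adds that "The α and power were taken as 0.05 and 0.8, respectively". The result follows directly: "A sample size of 35 participants was therefore calculated, with a target of 28 participants". Block size and "the estimated 20 % premature withdrawal rate of participants from the protocol" are named as having been taken into account.

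The paragraph does not say whether the SD is between persons, within person or of the paired difference. It also omits the sidedness of the test, the block size and the baseline LDL-C to which 7.4% refers. The same section plans a Bonferroni adjustment for comparisons between diets. The design is a four-period crossover, so each participant receives all four diets.

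The only LDL-C level given for the study population is in the section on inclusion criteria: "LDL-C >2.7 mmol/L", one of five criteria of which at least two must be met.

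**The concern.** A difference of 0.43 with an SD of 0.13 is a standardised effect of 0.43/0.13 = 3.3. An effect that large needs only a handful of participants in a crossover, yet the paragraph presents 28 as the consequence of these inputs.

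This paragraph is the article's only quantitative justification of the trial's size. If the inputs and the result do not belong together, a reader cannot tell which LDL-C difference the trial was planned to detect, or with what power.

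A second, weaker doubt concerns the pairing of 7.4% with 0.43 mmol/L, which implies a high mean LDL-C.

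**Working it through.** **Inputs (sample-size paragraph).** Difference δ = 0.43 mmol/L; SD = 0.13 mmol/L; alpha 0.05, taken as two-sided; power 0.80; 28 completers; 35 enrolled; 20% withdrawal.

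**Step 1: the withdrawal step.** 28/(1 − 0.20) = 35. This reproduces.

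**Step 2: the 28 completers.** For a comparison of two diets within persons, the normal approximation is n = (SD_d × (1.960 + 0.842)/δ)², where SD_d is the SD of the paired difference. With so few participants the exact paired t-test (noncentral t, n − 1 degrees of freedom) is the proper figure.

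| Reading of 0.13 | SD_d | n, normal approx. | n, exact t | n, exact t at 0.05/6 |
|---|---|---|---|---|
| SD of paired difference | 0.13 | 0.72 | 3 | 5 |
| Within-person SD per diet | 0.13 × √2 = 0.184 | 1.43 | 4 | 6 |

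Four diets form 4 × 3/2 = 6 pairs, hence 0.05/6 = 0.0083 in the last column. One-sided testing does not raise any of these numbers. A parallel two-group design would need 3 per arm by the t-test. None of these is near 28.

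**Step 3: were the two figures transposed?** With δ = 0.13 and SD 0.43, the exact t-test needs 88 completers (SD of differences) or 174 (within-person SD). That does not give 28 either.

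**Step 4: what 28 completers imply.** At n = 28, 80% power with a two-sided alpha of 0.05 corresponds to a standardised paired difference of 0.549.
- SD of differences needed at δ = 0.43: 0.43/0.549 = 0.78 mmol/L, and 0.78/0.13 = 6 times the stated SD.
- Detectable difference if 0.13 is the SD of differences: 0.549 × 0.13 = 0.07 mmol/L.
- Detectable difference if 0.13 is the within-person SD: 0.549 × 0.184 = 0.10 mmol/L.
- Power at n = 28 for δ = 0.43: above 99.9% under either reading.

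**Step 5: 7.4% against 0.43 mmol/L.** The two agree at a mean LDL-C of 0.43/0.074 = 5.81 mmol/L. The article gives no expected mean. At assumed means of 2.7 to 4.5 mmol/L, 7.4% is 0.074 × 2.7 = 0.20 to 0.074 × 4.5 = 0.33 mmol/L. Using those differences with SD 0.13 still needs only 4 to 9 completers at alpha 0.05, and at most 14 at 0.05/6. Dropping 0.43 in favour of 7.4% therefore does not recover 28.

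**Step 6: readings that do land near 28.** Each needs an assumption that the article does not state.
- If 0.13 is a standard error from about 35 persons, the SD is 0.13 × √35 = 0.77, and the paired t-test at 0.43 needs 28.
- If 0.13 stands for 13%, then 7.4/13 = 0.569 and the paired t-test needs 27.

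**The case against.** The strongest reply is that 28 may come from a sound calculation that was badly transcribed, and that the number enrolled is then right. Step 6 shows this is possible. But at least two different transcription errors lead to about 28, and the article does not allow a choice between them. The printed calculation stays wrong until the sponsor says what was meant. Block size does not explain it either: none is given, and rounding 3 to 6 up to complete blocks is not a plausible route to 28.

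Four stronger readings may tempt a reader, and the document does not support them.

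- *The trial is underpowered.* The printed inputs imply the opposite. True power depends on an SD and a difference that the article does not reliably give.
- *7.4% and 0.43 mmol/L contradict each other.* They do so only if mean LDL-C is not near 5.8 mmol/L. The criterion of 2.7 is an optional floor without a ceiling, and excluding users of lipid-lowering drugs could raise the mean. This is a serious doubt and belongs in a query.
- *HOCO-DHA has no LDL-C effect to plan on.* In the Background, the results that "were significantly reduced, and HDL was increased, after consumption of HOCO-DHA compared with regular canola and control diets" do not include LDL-C. The same section, however, reports an LDL-C reduction with HOCO and says the later trial confirmed those findings. Absence from a summary list does not show a null result, and the test oil is 85% HOCO.
- *A null LDL-C result could not be interpreted.* Its confidence interval would still show which differences are excluded, whatever the planning text says.

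**Conclusion.** Wrong as written. The printed difference, SD, alpha and power lead to 3 or 4 completers, or 5 to 6 with Bonferroni over six pairs, against the 28 stated. The gap in the SD is about sixfold (0.78 against 0.13 mmol/L). Only the step from 28 to 35 is correct. The claim of 80% power is therefore unsupported; whether actual power is higher or lower cannot be determined from the article.

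This rests on a within-person comparison of two diets by a two-sided paired t-test. It holds for either within-person meaning of the SD, and the one-sided, Bonferroni, transposed and parallel-group variants do not rescue it. The mismatch between 7.4% and 0.43 mmol/L remains a query, because no baseline mean is given.

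**What to change.** Restate the sample-size paragraph with one consistent set of inputs:

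1. The expected LDL-C difference in mmol/L for HOCO-DHA against control oil, with the baseline mean used. Confirm whether 7.4% or 0.43 mmol/L was intended.
2. The SD, labelled by type (preferably of the within-person difference), with its source. Check against the original calculation whether 0.13 is an SD in mmol/L, a standard error or a percentage.
3. The power, or the detectable difference, that 28 completers give at the significance level actually used after the planned Bonferroni adjustment, naming the number of comparisons.

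The cost is one paragraph and a look at the original calculation. It requires no added participants. The drawback is that the stated power may fall, or the detectable difference may grow, once the inputs are corrected.

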**Fig. 1 Fig1:**
[figure not shown]
Schematic representation of the experimental protocol. *Procedures are the same as in phase 1. *Blood* 12-h fasted blood collection, *ANTH* anthropometric measurements, *BP* blood pressure, *IE-CRIT* inclusion and exclusion criteria, *Qs* questionnaires (fish and seafood consumption, concomitant medications, adverse events, physical activity), *3D-FR* 3-day food record collection, *DEXA* dual-energy X-ray absorptiometry, *PHYS* physician examination, *GI* gastrointestinal questionnaires, *STOOL* stool sample collection, *D*
_*2*_
*O* deuterated water

Diets will be planned for every participant according to individual energy requirements and will be nutritionally adequate. Basal energy requirement will be estimated using the Mifflin-St Jeor equation [40]. The basal energy requirements will be multiplied by an activity factor of 1.7 to supply the additional energy needs of mildly to moderately active healthy adults. During the study period, body weight will be monitored. If any of the participants gain or lose weight during the first week, adjustments to their estimated energy requirements will be made. Participants will be given recommendations to follow a typical Western diet that meets the Canadian Dietary reference intake. The nutrient content of the participant’s diet, based on the 3-day food record, will be analyzed using Food Processor Nutrition Analysis software (ESHA Research, Salem, OR, USA) to ensure the intake of macro- and micronutrients and compliance with the protocol. Treatments will be isocalorically incorporated into muffins and cookies and consumed at breakfast, in the evening, as snacks, and with supper. Recruited participants will be randomly assigned to one of the treatment sequences using a Latin square design. Participants will be required to consume one muffin along with their breakfast and two cookies during their evening snack and dinner, respectively.

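### A before-after ANOVA is assigned to determine treatment effects alongside the between-diet mixed model, with no statement of which decides, and the mixed model leaves out the phase baseline

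*Protocol article*

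**What the plan says.** The section on sample size and statistical analysis names two analyses for treatment effects.

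- First: "Baseline and endpoint measurements will be compared using the analysis of variance (ANOVA) model for determination of treatment effects".
- Then, for the effects of the diets, a "mixed-model ANOVA with diet, sequence, phase, and center as fixed factors and subject as a random factor within the model", followed by: "Significance between different dietary effects will be examined with the Bonferroni adjustment for multiple comparisons".

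The text does not say which of the two decides, or whether the response in the mixed model is the endpoint or the change from baseline. No baseline term is among the listed factors. Yet the Sample collection section defines a lipid baseline and a final value for every phase: "average values of days 1 and 2 will be considered as baseline and average values of days 29 and 30 will be considered as the" final value.

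The trial is a crossover of "four phases with 28 days per phase, and each phase will be separated by 4-week washout periods". Participants are "randomly assigned to one of the treatment sequences using a Latin square design", and one of the four diets is a control (all-purpose flour with control oil). The sample size is framed on HOCO compared with control. The model lists center as a factor, but the Design section names one site: the trial "will be conducted at the Clinical Nutrition Research Unit".

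**The concern.** A change from baseline to endpoint on one diet contains the diet's effect plus everything else that changes during a phase. The Design section gives all four phases supervised meals, individually planned diets, dietary recommendations and an instruction to take no alcohol. Any shift these cause appears on all four diets.

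If the before-after ANOVA counts as determining treatment effects, a significant LDL-C change on one diet could be reported as an effect of that diet even when it does not differ from control. The trial's own question is a comparison with control, which only a between-diet contrast answers.

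A second, smaller matter is precision. A baseline is collected in every phase, and the listed model does not use it.

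**Working it through.** **Inputs from the article.** Target of 28 completers; four phases; Latin-square sequences; SD 0.13 mmol/L; planned LDL-C difference 0.43 mmol/L. The article gives no figure of its own for this point to reproduce.

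**Assumptions.** The 0.13 is taken as the within-person SD of a baseline or endpoint value, since the article does not say which SD it is. The correlation r between baseline and endpoint in a phase, after removing the participant effect, is not given and is varied. So is the shift shared by all diets.

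**Step 1: what each analysis estimates.** Write the endpoint as participant + phase + shared shift + diet effect + error, and the baseline as participant + phase + error.

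- Endpoint minus baseline on one diet estimates shared shift + diet effect.
- Endpoint on diet A minus endpoint on diet B, with phase in the model, estimates the difference in diet effects. The shared shift cancels.

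**Step 2: size of the before-after problem.** The SE of the mean change on one diet is 0.13 × √(2(1−r)) / √28.

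- r = 0: 0.1838 / 5.29 = 0.0347. A shift of 0.05 is 1.44 SE; a shift of 0.10 is 2.88 SE.
- r = 0.5: 0.13 / 5.29 = 0.0246. The same shifts are 2.04 and 4.07 SE.

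The simulation had no diet effect, a balanced 4 × 4 Latin square, a phase trend of 0.05 mmol/L per phase and 1,000 trials per setting. Percentage significant at 0.05:

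| r | Test | Shift 0 | Shift 0.05 | Shift 0.10 |
|---|---|---|---|---|
| 0 | before-after, one diet | 5.4 | 30.1 | 79.7 |
| 0 | diet contrast, no baseline | 4.8 | 5.3 | 4.7 |
| 0.3 | before-after, one diet | 5.6 | 38.5 | 92.3 |
| 0.3 | diet contrast, no baseline | 5.4 | 5.4 | 5.1 |
| 0.5 | before-after, one diet | 4.2 | 49.2 | 97.8 |
| 0.5 | diet contrast, no baseline | 4.1 | 5.3 | 4.3 |

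The mean estimate of the diet contrast lay between −0.0024 and 0.0012 mmol/L throughout. A shift of 0.10 is under a quarter of the planned 0.43 (0.10 / 0.43 = 0.23). The before-after rates depend only on the ratio of shift to SD: if the SD were 0.26, a shift of 0.10 would give the 0.05 column.

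**Step 3: what the baseline would add.** Relative to analysing the endpoint alone, the SE of a diet contrast is multiplied by √(1−r²) with the phase baseline as covariate, and by √(2(1−r)) with change scores.

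| r | Covariate | Change score |
|---|---|---|
| 0 | 1.00 | 1.41 |
| 0.2 | 0.98 | 1.26 |
| 0.3 | 0.95 | 1.18 |
| 0.5 | 0.87 | 1.00 |
| 0.7 | 0.71 | 0.77 |

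The covariate form is never worse than either alternative, apart from the degrees of freedom: 1−r² ≤ 1, and 1−r² = (1−r)(1+r) ≤ 2(1−r). In the simulation the empirical SE fell by 4 to 5% at r = 0.3 and 11 to 12% at r = 0.5. At r = 0 it rose by about 1%.

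**Step 4: center.** One site means one level. The term is redundant and changes no diet estimate.

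**The case against.** The strongest reply is that the valid analysis is already in the same section: diet, sequence and phase fixed, participant random, in a Latin-square crossover with a control diet. That stands, and it limits the point. A reader might infer that leaving the baseline out of the mixed model lets drift pass for a diet effect. It does not: shared drift cancels from the diet contrasts, and the simulation shows this with the baseline omitted. The risk lies only in the before-after sentence.

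It may also be said that this sentence merely means that change per phase is the response, and that an article leaves such detail to the analysis plan. Either may be so. If change is the response, the baseline is already used, though less efficiently than as a covariate. But the article is not silent: it gives the before-after comparison a purpose, and the Bonferroni sentence covers differences between diets only.

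Three further inferences are not supported.

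- **Error rate.** Four before-after tests at 0.05 would give 1 − 0.95⁴ = 18.5% chance of at least one false result. The article does not say that four such tests will be run, and the figure assumes independence.
- **Regression to the mean.** Eligibility rests on a separate screening sample, and each phase has a fresh two-day baseline, so most of the regression should come before the first phase baseline.
- **Carry-over.** Nothing in the article shows that residue survives the 4-week washouts.

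**Conclusion.** The point holds in a limited form. The plan gives a before-after ANOVA the task of determining treatment effects, beside a sound between-diet model, and does not say which decides. With no diet effect, an assumed shared shift of 0.05 mmol/L makes the before-after test significant in 30 to 49% of trials, and 0.10 mmol/L in 80 to 98%, for r from 0 to 0.5 and a within-person SD of 0.13. The mixed-model contrasts are unaffected.

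Omitting the phase baseline is a valid choice that introduces no bias. The precision forgone is conditional: none at r = 0, about 5% of the SE at 0.3 and about 13% at 0.5. Without r, a definite loss of precision cannot be claimed. Listing center is an editorial error.

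**What to change.** 1. State that between-diet contrasts from the mixed model on the phase endpoint decide, and that before-after changes within a diet are descriptive only. Remove the determination of treatment effects from the baseline-versus-endpoint sentence.
2. For outcomes with a phase baseline, add it as a covariate in two parts: the participant's mean baseline and the phase's deviation from that mean. The split keeps between-person differences from distorting the within-person slope. Outcomes measured only at the end of a phase, such as the cholesterol fractional synthesis rate, take no such term.
3. Delete center from the model.

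The cost is analysis wording and one or two degrees of freedom. With 28 completers and four phases there are 112 endpoints; after 28 participants, 3 phase terms and 3 diet terms, 112 − 34 = 78 within-person degrees of freedom remain, or 77 with the phase deviation. The participant mean uses one between-person degree of freedom. The lipid baselines needed are already planned.
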